### Stress-Related Survey Instruments

In addition to measuring cognitive performance and physiological changes, self-reports of stress will be measured throughout the experiment. To characterize the baseline level of stress, the State-Trait Anxiety Inventory (STAI) (Spielberger et al., 1983) and the Perceived Stress Scale (PSS-10) (Cohen et al., 1983) will be administered before the experimental session. Throughout the experiment, participants will answer a single-question ecological momentary assessment of perceived stress (Likert scale 1-7) and the State component of the short-form of the State-Trait Anxiety Inventory (STAI-6) (Marteau and Bekker, 1992) to dynamically rate their stress levels. These survey responses allow for characterizing changes in the participant’s perceived stress levels compared to the cognitive performance and physiological responses. As an exploratory analysis, surveys regarding job satisfaction (Russell et al., 2004) and the Ten Item Personality Inventory (TIPI) (Gosling et al., 2003) will be distributed before each experimental session to examine how physiological signals during the stress task are related to participants’ general personalities.

### Statistical Analyses

#### Planned Statistical Analyses

Summary statistics of demographics (Age, Sex, Ethnicity, Education) and baseline characteristics (Trait level of Anxiety and Stress) of participants will be reported for all participants in the study (separated by the main and the optimization period). Cognitive performance metrics and survey responses will be analyzed using univariate mixed-effects models. Descriptive statistics, generalized estimating equations (GEEs), and power spectrum analysis will be used to analyze the wearable-collected physiological data. Generalized estimating equations will also be used to fit each of the physiological measures (HR, HRV, and EEG) and compare across the different epochs of the experiment. As an additional analysis, we will use univariate mixed-effects models to understand how physiological, subjective and cognitive measures correlate and differentiate the different cohorts, providing an overall view on how these features combine to represent the recovery after stress.

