Prior studies have demonstrated naturalistic sensory stimuli are effective at promoting recovery after stress (Yin et al., 2020). Experiencing visual and auditory elements from nature has been shown to reduce stress and improve mood (Shibata and Suzuki, 2004; Fuller et al., 2007; Park et al., 2009; Brown et al., 2013; Hedblom et al., 2019). Physiological benefits in relation to heart rate and neural activity also occur after experiencing naturalistic visual and auditory stimuli (Jo et al., 2019; Yin et al., 2020). Cognitive performance has also been shown to be adversely affected by stress but can be improved when exposed to biophilic environments (Shields et al., 2016; Yin et al., 2018). Taken together, we hypothesize that physiological measures and cognitive performance after a stressful event will return to pre-stress levels faster when experiencing both auditory and visual stimuli of the MindBreaks room compared to only auditory or visual stimuli or neither.

The objective of this study protocol is to determine whether different visual and/or auditory features of a relaxation room affect the recovery of physiological signals, cognitive function, and perceived stress after an experimentally controlled acutely stressful event. Understanding how different sensory features promote recovery after stress could lead to an individual- and organization-level approach for using relaxation rooms to mitigate the effects of workplace stress and burnout.

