Our selection of HRV metrics is based on a meta-analysis examining HRV in acute mental stress done by Castaldo et al. (2015). Given that time-domain HRV metrics, Mean RR, SDNN, RMSSD, and pNN50 have been shown to be affected by acute stress (Castaldo et al., 2015), we will compare these metrics before, during, after stress to determine when it recovers to baseline levels. Similarly for the frequency domain, HF has been shown to decrease during stress (Castaldo et al., 2015; Shaffer and Ginsberg, 2017), so we will compare the HF of HRV metrics before, during, and after stress to determine when HF power increases back to baseline levels. As exploratory, *post hoc* analyses, we will also look at VLF of HRV to determine if there are any task-related changes after stress. Usui and Nishida (2017) has shown that VLF slowly recovered after a mental task compared to HF, thus it would be worth to examine whether existence of sensory features could promote the recovery process of VLF.

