Electroencephalography analyses will be conducted mainly in python using the MNE toolbox (Gramfort et al., 2013). As the primary outcome, we will compare alpha spectral power (8-13Hz) before, during, and after the stress epoch, as this has been shown to significantly decrease in response to a stressor (Vanhollebeke et al., 2022). As exploratory analyses, we will compare spectral power before, during, and after the stress epoch in the theta (4-8Hz), beta (13-32Hz), and gamma/high-gamma (32-100Hz) frequency bands similar to Arsalan and colleagues (Arsalan et al., 2019), as well as frontal alpha asymmetry similar to prior studies (Quaedflieg et al., 2015; Ehrhardt et al., 2021; Hu et al., 2021). The lateralized reference in the Dreem headband (FP2) will be taken into consideration when interpreting any frontal alpha asymmetry results, as this could produce false positive results. Although these exploratory analyses were not shown to have significant responses to a stressor based on the meta-analysis conducted by Vanhollebeke and colleagues (Vanhollebeke et al., 2022), the focus here will be on whether neural activity in these frequency bands significantly modulates in response to the stressor and the specific sensory stimuli during the recovery epochs, which to our knowledge has not been previously examined.

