### Cognitive Assessments

Participants will perform cognitive assessments to assess working memory function at specific times during the stress induction task. Acute stress has been shown to affect performance on working memory tasks (Vedhara et al., 2000; Shields et al., 2016; Jiang and Rau, 2017). In this study, participants will use a cognitive assessment application designed by the Well Living Lab (Jamrozik et al., 2019; Aristizabal et al., 2021a) to perform two working memory tasks: the Operation Span (OSPAN) task and the Symmetry Span (SSPAN) task (Foster et al., 2015; Draheim et al., 2018). Participants will perform these assessments on a 12.9” iPad Pro (*Apple Inc., California, United States*) located on a desk to ensure consistent placement across participants. Although some studies have required 85% accuracy on the processing components of the task (math accuracy for OSPAN, symmetry accuracy for SSPAN), other studies have found similar task performance measures without requiring such a processing accuracy threshold (Đokić et al., 2018). To ensure we have cognitive measures for each time step in the TSST (outlined in Figure 2), we will not require a processing accuracy threshold when analyzing changes in cognitive performance.

Two dependent measures will be used for analysis of both SPAN tasks: Unit Score and Load Score. The Unit Score is the average of the proportion of letters or grids participants can recall correctly in the appropriate order in each set. The Load Score is calculated from the sum of correctly recalled elements from all trials, regardless of the order. Both scores will be used to assess changes in working memory capacity before and after the stress induction task.

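### The main physiological analyses are stated as within-person epoch comparisons, but the hypothesis is a between-cohort difference in speed of recovery

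*Protocol article*

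**What the plan says.** - **Hypothesis (Introduction).** Physiological and cognitive measures "will return to pre-stress levels faster when experiencing both auditory and visual stimuli of the MindBreaks room", compared with auditory only, visual only or neither.
- **Main physiological model (Planned Statistical Analyses).** GEEs will "fit each of the physiological measures (HR, HRV, and EEG) and compare across the different epochs of the experiment". Cohort is not named in that sentence.
- **HRV (Cardiac Measures).** For the time-domain metrics, "we will compare these metrics before, during, after stress to determine when it recovers to baseline levels". High-frequency power is handled in the same way, "to determine when HF power increases back to baseline levels".
- **EEG (Neural Activity).** For the primary EEG outcome, "we will compare alpha spectral power (8-13Hz) before, during, and after the stress epoch".
- **Cohorts (Planned Statistical Analyses).** They appear only in an additional analysis by mixed-effects models, "to understand how physiological, subjective and cognitive measures correlate and differentiate the different cohorts".
- **Span tasks (Cognitive Assessments).** "Both scores will be used to assess changes in working memory capacity before and after the stress induction task". The Power Analyses section sizes the trial for a mixed model that compares two experimental conditions directly.
- **Intent.** The Abstract (Methods) says that the before/after comparison is meant to show how the stimuli affect the rate of recovery. The Neural Activity section twice links recovery to the features of the room.

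**The concern.** The question concerns four randomised groups, but the comparison named for the main physiological outcomes is of each participant with themselves. A change between epochs shows that the stressor worked and that signals came back. It does not show that they came back faster in one room condition than in another.

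The article does more than leave out a model term. It states a comparison (epochs) and a question (when is the metric back at baseline), and both differ from the hypothesis. The Abstract then presents the before/after comparison as the route to the conclusion about stimuli. An analyst who followed this text could report the central result without a test of the cohort difference at a known error rate.

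**Working it through.** **1. Contrast needed and contrast stated**

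| Outcome | Needed by the hypothesis | Stated |
|---|---|---|
| HR | audio-visual v each other cohort, speed of recovery | GEE, across epochs |
| Time-domain HRV, HF | same | before/during/after; when back at baseline |
| Alpha power | same | before/during/after |
| All measures together | same | additional analysis that differentiates cohorts; no recovery measure, no audio-visual contrast |

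If the epoch comparison is pooled over cohorts, it carries no information on cohort differences. If it is made within each cohort, a conclusion about cohorts has to come from setting one cohort's significance result beside another's.

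**2. The plan's own figure**

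The Power Analyses section gives 18 per group for 80% power at 1 SD, significance level 0.05 (two-sided assumed). By the normal formula, n = 2(1.960 + 0.842)² × 1² / 1² = 15.7, so 16; with the t distribution, 17. Power at 18 is 0.85 (normal) or 0.83 (t). The stated 18 is thus close to a plain comparison of two conditions. The point does not rest on it, but it shows that a between-condition contrast was in mind.

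**3. Illustration of the within-cohort route**

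Inputs from the plan: 20 per cohort (Recruitment), level 0.05 and correlation 0.3 (Power Analyses; stated there for the cognitive measures and borrowed here). Assumptions: one recovery time point, two-sided paired t-test against baseline, all four cohorts truly identical, and a remaining deviation d of 0.3, 0.5 or 0.7 SD.

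- SD of a change score = √(2(1 − 0.3)) = √1.4 = 1.183.
- Noncentrality = (d / 1.183) × √20, giving 1.13, 1.89 and 2.65. The critical t on 19 df is 2.093.
- p = chance that one cohort's test is significant.
- Chance that audio-visual is non-significant and at least one of the other three is significant = (1 − p) × [1 − (1 − p)³].

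| d (SD) | p | Audio-visual back, at least one other not | Audio-visual back, control not: (1 − p)p |
|---|---|---|---|
| 0.3 | 0.190 | 0.81 × (1 − 0.81³) = 0.38 | 0.15 |
| 0.5 | 0.434 | 0.566 × (1 − 0.566³) = 0.46 | 0.25 |
| 0.7 | 0.709 | 0.291 × (1 − 0.291³) = 0.28 | 0.21 |

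Outside that range the figure is lower: 0.135 at d = 0 and 0.05 at d = 1.0. Requiring all three other cohorts to remain significant gives 0.006, 0.046 and 0.104 at d = 0.3, 0.5 and 0.7. A direct cohort-by-time test holds each contrast at 0.05, so the chance of any false positive among three is at most 3 × 0.05 = 0.15.

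**4. Does the direct contrast fit the sample size?**

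For a 1 SD difference at one recovery time point with correlation 0.3:

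- Change from baseline: variance factor 2(1 − 0.3) = 1.4; n = 15.7 × 1.4 = 22 per group; power 0.74 at 20.
- Baseline as covariate: variance factor 1 − 0.3² = 0.91; n = 15.7 × 0.91 = 14.3, so 15; power 0.86 at 18 and 0.90 at 20.

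The adjusted contrast fits within 20 per cohort.

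**The case against.** The strongest reply is that the comparison of conditions is plainly intended. The Abstract and the Neural Activity section say so, the Power Analyses section is built on two conditions compared directly, and the additional analysis does concern cohorts. This is also a condensed article, and a fuller analysis plan may hold the interaction term. All of this stands as evidence of intent. It does not turn that intent into a stated physiological test: where the article names the comparison for those outcomes, it names epochs.

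Four stronger readings are tempting, and the documents do not support them:

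- *The plan will date recovery at the first non-significant time and rank cohorts by it.* No decision rule, separate test per cohort or ranking is stated. The rates above show what the wording permits, not what is planned.
- *No cohort comparison is planned.* One is, as an additional analysis.
- *Every metric is judged by when it is back at baseline.* That wording covers only time-domain HRV and high-frequency power. Alpha power is compared before, during and after stress, and HR is covered by the GEE sentence.
- *Practice effects undermine the span-task results.* Repeated testing does mix practice with recovery in a before/after change, but practice shared by randomised cohorts cancels in the two-condition comparison assumed in Power Analyses.

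**Conclusion.** The point holds as a mismatch between the stated hypothesis and the stated main physiological analyses. The mismatch is read directly from the text and needs no assumption. The 28% to 46% is illustrative: it depends on identical cohorts, one recovery time point, correlation 0.3, a residual of 0.3 to 0.7 SD, and a reader who treats non-significance against baseline as recovery. It should not be quoted as the error rate of this trial. For the span tasks only a small point remains: conclusions should rest on the comparison of conditions and not on before/after change alone.

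**What to change.** - In Planned Statistical Analyses, state that for each physiological outcome the test of the hypothesis is the cohort-by-time (epoch) contrast over the recovery period in the planned GEE, adjusted for the pre-stress level. Report audio-visual against each of the other three cohorts with a 95% CI.
- Align the HRV text under Cardiac Measures and the alpha-power text under Neural Activity with that sentence.
- Label epoch-versus-baseline comparisons as a descriptive check that the stressor worked.
- For OSPAN and SSPAN, state that conclusions rest on the between-condition contrast already assumed in Power Analyses.

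The cost is wording: same data, same model families, no added burden on participants. If the three contrasts are to share the 0.05 level (0.05/3 each), power for an unadjusted comparison at 1 SD is 0.68 with 18 and 0.74 with 20 per group, so that choice should be made knowingly.

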#### Power Analyses

Sample size was determined based on the 5 cognitive performance measures, which were the least frequent measure collected during each experimental session, with an assumption of using a univariate mixed effects model with 5 measurements per participant, significance level of 0.05, moderate correlation between repeated measures (0.3), and directly comparing two experimental conditions instead of all conditions at once. Powering based on the least frequent measure ensured that we were sufficiently powered when analyzing the other measures in the study. We would reach 80% power with 18 participants per group with a mean difference of 1 standard deviation. Including 20 participants per group will provide a buffer for potential drop-out.

## Discussion

We anticipate the findings from this study will have a wide impact ranging from the scientific community to institutions looking for effective organizational strategies for mitigating workplace stress and burnout. The study optimization from 20 participants is being conducted between December 2021 and March 2022 to test and finalize the study parameters and procedures. Recruitment for the main trial (*n* = *80*) is expected to start in March 2022 and will continue until December 2022 or until enrollment is completed. Participants will be randomly assigned to one of four cohorts and data are collected throughout this period. Final data collection and subsequent analysis are anticipated by December 2022. We expect all trial results will be available by early 2023.

A socially evaluating situation can be stressful for the most individuals. The TSST is a powerful technique for eliciting a stress response in an experimentally controlled environment. However, there are other factors that might contribute to stress responses in a real working environment that might not be captured in the TSST. There are several factors that play a role in workplace stress, including working environment and workload, the role of the employee (and any ambiguity in that role), or the organizational climate (Colligan and Higgins, 2006). An individual’s job function, such as working in a managerial position or in public relations, might also have differing levels of workplace stress that might not be fully captured by the TSST. Even with this potential limitation, the results from this study can provide valuable insights how individuals recover from acutely stressful situations. Understanding how relaxation rooms mitigate responses after acute stress could provide insight into which physiological and cognitive measures to monitor when attempting to detect and mitigate chronic workplace stress and burnout in real workplace environments.

Other potential pitfalls or unintended effects may come from each participants working position which has been shown to have differing levels of stress (Colligan and Higgins, 2006). Additionally, Xin and colleagues have shown that personality index also correlates with response after acute stress (Xin et al., 2017) which could also play a factor in how each cohort responds. Although we cannot statistically power for each of these factors, we will record information about each of them from each participant to examine in *post hoc* exploratory analyses.

Performing the cognitive tasks might induce additional stress by itself, however, we will attempt to characterize this stress due to the cognitive task by analyzing the physiological measures during the cognitive task at baseline and at the end of the recovery epoch. Additionally, we are assuming that the findings from this study can be extended to understand how longitudinal use of a relaxation room might mitigate the adverse effects of burnout and workplace stress. Future studies are needed to test these assumptions as the physiological and cognitive responses after acute stress might differ from chronic stress.

The strength of this proposed study is the ability to examine how effective different sensory features of a relaxation room are at promoting recovery of physiological signals, cognitive function, and perceived stress after a highly controlled stress induction task. Using multiple wearable devices to acquire various types of physiological signals including heart rate and neural activity as well as using two different working memory tasks to characterize cognitive performance allows us to acquire high-resolution information about how stress influences each individual. These findings could ultimately lead to improved individualized and organizational approaches to mitigating workplace stress and burnout.

## Ethics Statement

This study involving human participants was reviewed and approved by The Mayo Clinic Institutional Review Board in September 2021, under the number 21-005885. The patients/participants provided their written informed consent to participate in this study.
